### Statistical analysis

To analyse the data SPSS (Statistical Package for the Social Sciences, Chicago, Illinois) will be used. A *p*-value of < .05 will be considered to indicate statistical significance. Descriptive statistics (means and standard deviations) will be used to describe the subject characteristics and the results of the groups. The PASS score is determined by assessing the score on the HOOS of patients who are satisfied with their actual physical state and symptoms. PASS scores will be determined for the measurements made at six weeks, three months and one year postoperatively. The satisfaction question, which is asked on a four-response Likert scale, will be dichotomized into “satisfied” (i.e. the patients who are “very satisfied” or “somewhat satisfied”) and “unsatisfied” (i.e. the patients who are “somewhat dissatisfied” or “very dissatisfied”) [30, 32]. This dichotomized variable will then be used as anchor to calculate cut-off values on the HOOS to determine the PASS score. Next, a ROC analysis will be conducted, using the satisified/dissatisfied variable as anchor. As optimal cut-off value will be the one that maximizes the sum of sensitivity and specificity [30].

After that, all patients will be categorized as responders (i.e. a score on the HOOS beyond the PASS score) and non-responders. Chi-square tests will be used to determine potential differences in the proportion of responders between the study and control group at the above-stated time-points. Additionally, odds ratios with corresponding 95% confidence interval (CI) will be calculated. This ratio represents the odds of being a “responder” for the study group, compared to the control group. An odds ratio larger than 1 favours the study group and the point estimate of the odds ratio is considered to be statistically significant if the 95% CI does not include the value of 1.

Changes in physical activity, participation and gait function will be analyzed with Generalized Estimating Equations (GEE) analyses [51]. Analysis of Variance (ANOVA) will be used to assess differences in urine incontinence (ICIQ-SF), radiographic measurements, surgical time, blood loss and length of hospital stay between the study and control group. Differences in complication rates will be assessed by means of a Chi-square test.

For both the study and control group the mean costs, mean effects (measured with HOOS) and mean QALY (based on the utility scores of the EQ-5D) will be calculated. Next, mean costs, mean effects and mean QALYs are used to calculate the incremental costeffectiveness ratio (ICER) [52] by dividing the difference in costs by the difference in effects/QALYs between the study and control group. Uncertainty surrounding the calculated ICER will be examined by the bootstrap method. Incremental cost-effectiveness ratios will be calculated for each of the bootstrap iterations (5000 in the present study), which then will be combined to form a mean ICER with corresponding 95% CI.

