#### Physical functioning and health-related quality of life

Main study parameter is the Patient Acceptable Symptom State (PASS), which is an approach to measure patient’s responses to treatment. The concept of PASS is based on wellbeing or satisfaction with the actual symptoms and is defined as the value on a patient-reported outcome measure (PROM) beyond which patients consider themselves well [28, 29]. The use of PASS is therefore a simple way to determine whether a patient has achieved therapeutic success. PROMs estimate the effectiveness of healthcare delivered to patients as perceived by the patients themselves. The PASS score is determined by assessing the score on a PROM of patients who are satisfied with their actual physical state and symptoms. Based on patients’ satisfaction with symptoms, the optimal cut-off value of the used PROM can be determined [30–32]. In this study, PASS scores will be derived from scores on the Hip disabilities and Osteoarthritis Outcome Score (HOOS) [33], and they will be determined for the measurements made at two and six weeks, three months and one year postoperatively. The HOOS consists of 5 subscales; pain, other symptoms, function in daily living, function in sport and recreation, and hip-related quality of life. The last week is taken into consideration when answering the questions. The Dutch version of the HOOS is considered valid and reliable [33]. Additionally, the patients’ opinion about “actual satisfaction with their symptoms regarding their hip problem” will be asked with one question. This question will be “if you spend the rest of your life with the hip symptoms you have now, how would you feel?” A Likert version of this question will be used with four response levels: very satisfied, somewhat satisfied, somewhat dissatisfied and very dissatisfied [29, 30, 32]. The scores on this question are then used to calculate PASS. The PASS scores at the previous mentioned time points will each be compared with the preoperative state and then compared between the two approaches [30].

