### Sample size calculation

Escobar et al. [30] showed that 70% of patients achieved an acceptable symptom state (PASS) at three months following THA, which means they have a positive PASS. The hypothesis is that the anterior approach results in a larger proportion of patients with a positive PASS at three months following THA. A difference of 20% in the proportion of patients with a positive PASS between the anterior approach and the posterolateral approach is considered clinically significant, as is described is described in the OMERACT-OARSI criteria [50]. Hence, based on the results of Escobar et al., a sample size of 60 patients in each study subgroup is needed to detect this difference of 20%, with a power of 80% and an alpha of 5%. Hence, each arm of the RCT needs to contain 120 patients. Based on previous experience, it is expected that approximately 10% will be lost in the follow-up. Hence, the total sample size will be set at 260 patients.

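### The main study parameter is not fixed to one test: the HOOS score that defines a responder is not named, and the three-month comparison is not carried into the analysis

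*Protocol article*

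**What the plan says.** All references are to the protocol article.

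- **Physical functioning and health-related quality of life.** PASS is the main study parameter and is derived from the HOOS. The designation carries no time point. The instrument is described thus: "The HOOS consists of 5 subscales; pain, other symptoms, function in daily living, function in sport and recreation, and hip-related quality of life". No total score is defined. PASS is to be determined at four visits (two weeks, six weeks, three months, one year), and the approaches are to be compared at each.
- **Sample size calculation.** The only efficacy hypothesis with both a time point and an effect size is here: "The hypothesis is that the anterior approach results in a larger proportion of patients with a positive PASS at three months following THA". The assumed rate is that "70% of patients achieved an acceptable symptom state (PASS) at three months following THA", the difference of interest is 20 percentage points, power is 80% and alpha 5%.
- **Statistical analysis.** A general threshold of p<.05 applies. PASS is determined at three visits; two weeks is not listed. The cut-off comes from an ROC analysis of the trial's own data, after which "all patients will be categorized as responders (i.e. a score on the HOOS beyond the PASS score) and non-responders". Chi-square tests then compare responder proportions "between the study and control group at the above-stated time-points". Odds ratios are also given, each called significant if its 95% CI excludes 1. No visit is marked as primary.

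**The concern.** Two features of the main parameter are open.

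**The score.** With five subscales and no defined total, the responder definition does not determine who is a responder. The cut-off is estimated from the trial data, so each candidate score would have its own cut-off and its own set of responders. Two analysts following the text could reach different main results.

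**The visit.** Three months appears as the target only in the sample size section. The analysis section treats all its visits alike. The Measurements section expects the advantage mainly in early recovery, which offers a ready reason to put an earlier visit first.

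What is at stake is whether a positive main result carries a 5% error rate. The trial cannot blind patients to the approach and the outcome is self-reported, so a choice of score or visit made after the data are seen would be hard to defend.

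**Working it through.** **1. The plan's own figure.** Inputs from Sample size calculation: 70% against 90%, power 80%, alpha 5% (sidedness not stated; two-sided assumed).

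n per group = [z₀.₉₇₅·√(2·p̄·(1−p̄)) + z₀.₈₀·√(p₁(1−p₁)+p₂(1−p₂))]² / (p₂−p₁)², with p̄ = 0.80

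= [1.960·√0.32 + 0.842·√0.30]² / 0.04 = [1.109 + 0.461]² / 0.04 = 61.6, so 62.

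The unpooled form gives 58.9 and the arcsine form 59.0. The stated 60 per subgroup is therefore reproduced for **one** test at two-sided 5%. Power at 60 per group is 78.9% by the pooled formula.

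**2. Passages side by side.**

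| Feature | Measurement section | Sample size section | Analysis section |
|---|---|---|---|
| HOOS score used for PASS | not named; five subscales listed | not named | not named; singular wording |
| PASS visits | 2 weeks, 6 weeks, 3 months, 1 year | 3 months | 6 weeks, 3 months, 1 year |
| Primary visit | none stated | implied: 3 months | none stated |
| Threshold | – | alpha 5% | p<.05 for all tests |

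**3. Error rate if the open choices were used.** For k independent tests, the chance of at least one false p<.05 is 1 − 0.95^k:

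- k = 3 visits: 1 − 0.95³ = 14.3%
- k = 4 visits: 1 − 0.95⁴ = 18.5%
- k = 5 subscales at three months: 1 − 0.95⁵ = 22.6%

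The tests share patients, so independence is an upper reference. Correlated standard normal statistics were simulated (200,000 draws, equal correlation, counting any |Z| > 1.96). The documents give no correlations, so these are assumptions:

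| Open choice | Assumed correlation | At least one false p<.05, two-sided |
|---|---|---|
| 3 visits, one score | 0.7 to 0.3 | 11.0% to 13.6% |
| 4 visits, one score | 0.7 to 0.3 | 13.0% to 17.5% |
| 5 subscales, three months | 0.8 to 0.5 | 12.7% to 18.3% |
| One named score, three months | – | 5.0% |

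These count errors in either direction. By symmetry, about half favour the anterior approach. For one score with visit correlation 0.5 to 0.3, counting only Z > 1.96 gives 6.2–6.8% for three visits and 7.8–8.8% for four, against 2.5% for a single test.

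**4. Cost of adjusting instead of choosing.** Bonferroni over three visits (0.05/3 = 0.0167) needs 83 per group for 70% against 90% at 80% power, and power at 60 per subgroup falls from 78.9% to 63.9%. Over four visits the figures are 88 and 59.8%. Over five subscales at three months they are 92 and 56.7%. Naming one test leaves step 1 as it stands.

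**The case against.** The strongest reply is that the primary comparison can be read from the sample size section. That section ties the hypothesis, the 20-point difference, the power and the 5% alpha to three months, and a sample size section conventionally identifies the main comparison. On that reading the other visits are secondary and alpha across visits is 5%. This has real weight: the visit is implied, and the plan cannot be said to break its alpha. What remains is that neither the section naming the main parameter nor the analysis section repeats it, and both compare the arms at every visit on the same footing. Nor does it settle the score, so the 13–18% scenario stays open even with three months accepted.

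A reader might infer that the protocol plans 15 or 20 tests, five subscales at three or four visits, with an error rate of 30–50% or more. The documents do not support this. The analysis wording is singular, the economic section also treats the HOOS as one measure of effect, and the subscales are listed only to describe the instrument. The defect is an unspecified score, not a planned family of subscale tests.

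It may also be said that a condensed article leaves multiplicity rules to the analysis plan. That is fair for an adjustment method or the handling of secondary visits, and no fault is found there. It does not cover which score defines the main parameter, or two sections that list different visits for it.

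**Conclusion.** The point holds in this form: as written, the main parameter does not resolve to one test. The score is undefined, the primary visit is implied in one section and not carried into the analysis, and the two visit lists conflict. The 5% alpha is not guaranteed. If the open choices were used, the two-sided error rate would be about 11–14% (three visits), 13–17% (four visits) or 13–18% (subscale at three months), with about half of those errors favouring the anterior approach. These figures rest on assumed correlations of 0.3–0.7 between visits and 0.5–0.8 between subscales. They also suppose that any one success would be reported as the main result. They are not the error rate of a declared plan. The sample size is not at fault on this point.

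**What to change.** In the sections Physical functioning and health-related quality of life and Statistical analysis:

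1. Name one HOOS score, either a subscale or a defined total, as the basis of PASS responder status. The sponsor should choose it, with a reason, before any analysis by treatment arm. The documents do not favour a particular subscale.
2. State that the responder comparison on that score at three months is the single primary test, two-sided 5%.
3. Label all other scores and visits secondary, reported as estimates with 95% CIs and without confirmatory claims.
4. Reconcile the four-visit and three-visit lists, saying whether PASS is determined and compared at two weeks.

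The change is one of wording. The sponsor gives up confirmatory claims at other visits or on other subscales, including the early visits where most benefit is expected. The sample size stays as planned.

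### The primary PASS analysis names no difference in proportions with a confidence interval and takes no account of stem type, although the clinical criterion is a 20-point difference and allocation is separate by stem type

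*Protocol article*

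**What the plan says.** **Criterion and sample size (Protocol article, Sample size calculation).** The hypothesis is that "the anterior approach results in a larger proportion of patients with a positive PASS at three months following THA". The planning rate is that "70% of patients achieved an acceptable symptom state (PASS) at three months following THA". The threshold is explicit: "A difference of 20% in the proportion of patients with a positive PASS between the anterior approach and the posterolateral approach is considered clinically significant". From this it follows that "a sample size of 60 patients in each study subgroup is needed to detect this difference of 20" percentage points, and that "each arm of the RCT needs to contain 120 patients".

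**Analysis (Protocol article, Statistical analysis).** Each patient is classed as a responder or non-responder by a HOOS cut-off. Chi-square tests compare the proportion of responders between the two approaches at each time point. As an addition, "odds ratios with corresponding 95% confidence interval (CI) will be calculated". A ratio above 1 favours the anterior approach, and the ratio counts as statistically significant when its interval leaves out 1. No difference in proportions with an interval is named. No odds ratio corresponding to 20 points is given. Stem type does not appear in the test or the estimate.

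**Allocation (Protocol article, Study population and recruitment procedure).** Two separate random allocation sets are generated, one for uncemented and one for cemented femoral stems.

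**The concern.** The trial states what size of effect matters, on one scale, and then puts its only interval on another. An odds ratio has no fixed relation to a 20-point difference: the conversion depends on the control rate. That rate cannot be fixed in advance here, because the cut-off that defines a responder comes from an ROC analysis of the trial's own data. The planned reading rule (does the interval include 1?) shows whether there is evidence of any difference. It does not show whether the data support, exclude or leave open 20 points.

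With responder rates of 70% to 90%, the odds ratio is also much larger than the ratio of proportions, so a reader can easily take it for a bigger benefit than it is.

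Separately, randomisation is stratified by stem type, but the analysis as described is not. Stem type goes with bone stock and age, so responder rates may well differ between the strata.

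**Working it through.** **Inputs.** Control rate 0.70, difference 0.20, power 80%, alpha 5%, 60 per subgroup and 120 per arm, all from Sample size calculation. Assumption: alpha is two-sided (the article does not say).

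**1. Reproduce the plan's figure.** For 0.70 v 0.90 with pooled variance and no continuity correction:

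n = [1.96·√(2·0.8·0.2) + 0.842·√(0.7·0.3 + 0.9·0.1)]² / 0.20² = (1.109 + 0.461)² / 0.04 ≈ 61.6, so 62.

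Unpooled variance gives (1.96 + 0.842)²·0.30/0.04 ≈ 58.9, and the arcsine method gives 59.0. The stated 60 is reproduced. A 20-point gain from 60% would need 82, and from 50% it would need 93. The trial is therefore sized on an absolute difference of 70% v 90%.

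**2. Convert between scales.** OR = [p₁/(1−p₁)] / [p₀/(1−p₀)].

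| Control rate | OR equal to a 20-point gain |
|---|---|
| 50% | 2.33 |
| 60% | 2.67 |
| 70% | 3.86 |
| 75% | 6.33 |

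In the other direction, OR 3.86 is 29.4 points from 50%, 25.3 from 60%, 20.0 from 70% and 13.9 from 80%. At the planning rates the ratio of proportions is 0.90/0.70 = 1.29, against an odds ratio of 3.86.

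**3. Planning rates observed, 120 per arm (84 v 108 responders), Wald intervals.**
- Difference: SE = √(0.21/120 + 0.09/120) = 0.050, so 20.0 points (10.2 to 29.8).
- Odds ratio: SE of the log = √(1/84 + 1/36 + 1/108 + 1/12) = 0.364, so 3.86 (1.89 to 7.87).

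**4. Smallest significant result with 84 of 120 control responders (uncorrected chi-square).**
- 97 responders: z = 0.1083/√(2·0.7542·0.2458/120) = 1.95, not significant.
- 98 responders: z = 0.1167/√(2·0.7583·0.2417/120) = 2.11, significant.
- For 84 v 98 the difference is 11.7 points, with SE = √(0.21/120 + 0.1497/120) = 0.0548 and 95% CI 0.9 to 22.4.
- The odds ratio is (98/22)/(84/36) = 1.91, with SE of the log = √(1/84 + 1/36 + 1/98 + 1/22) = 0.309 and 95% CI 1.04 to 3.50.

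The article's rule calls this result significant in favour of the anterior approach. The difference interval adds that the estimate lies well below 20 points, and that the data fit anything from almost no benefit to slightly more than 20.

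**5. What stratification changes.** The Mantel-Haenszel difference is Σwₖ(p₁ₖ − p₀ₖ)/Σwₖ, with wₖ = n₁ₖn₀ₖ/(n₁ₖ + n₀ₖ). With the planned 60 v 60 in each stem stratum, each weight is 60·60/120 = 30, so the estimate equals the crude difference. Stratification then changes only the standard error and the test. If the stratum sizes differ between arms, it also removes that imbalance from the estimate.

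**The case against.** The strongest reply is that the plan does work with proportions. The chi-square test comes first and compares responder proportions, which is the scale of the hypothesis. The odds ratio is introduced as an addition. Both measures come from the same 2×2 table, so the control rate will be known and anyone with the responder counts can compute the difference and its interval. The sentence about 1 defines statistical significance correctly and does not claim clinical relevance. A significant result smaller than the planning difference is possible under any superiority test. An analysis plan that is not shown may add the difference.

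Most of this stands. A reader might infer that the effect will be reported only as an odds ratio, and that the result therefore cannot be judged against 20 points. The article does not support that: it tests proportions and nowhere says they will be withheld. A reader might also infer that the trial will claim clinical relevance whenever the interval excludes 1. The article does not say that either.

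What does not fall is narrower. A chi-square test gives a p-value and no estimate. The article chose an effect measure, gave it an interval and a reading rule, and that choice does not match the criterion in its own Sample size calculation. The stated comparison also does not use the allocation strata. These are choices made in the text and not details merely left to another document.

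**Conclusion.** The point holds as a modest improvement to a stated analysis. The only PASS estimate with an interval is on a different scale from the 20-point criterion and is read only against 1, and the described test and estimate leave out the stem-type strata. In size, a result can be significant at 11.7 points (84 v 98 of 120, 95% CI about 1 to 22), and the planning effect of 20 points appears as an odds ratio of 3.86.

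The test as planned is valid, the sample size is reproduced, and the result stays readable from the counts. The conclusion assumes a two-sided alpha, 20% read as absolute points (supported by reproducing 60 per subgroup), 120 analysed per arm and, for the example, a control rate of 70%.

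**What to change.** In the Statistical analysis section or the analysis plan, before the comparison is run:

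- Name the three-month difference in the proportion with a positive PASS (anterior minus posterolateral), with its 95% CI, as the main effect estimate.
- Combine it over the cemented and uncemented strata with Mantel-Haenszel weights, and use the matching stratified (Cochran-Mantel-Haenszel) test.
- Report the responder counts per arm and stratum.
- State whether the interval lies below, includes or lies above 20 points. This should be a description and not a success criterion: even at the planning rates the lower limit is about 10 points, so the trial is not sized to show that the difference exceeds 20.
- Keep the odds ratio as a secondary summary.

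The cost is a few sentences of wording and a small addition to the output. No new data and no change in sample size are needed.

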#### Perioperative measurements

Surgical time, rate of complications, position of the femoral and acetabular components and length of hospital stay will be recorded. Position of the femoral and acetabular components will be measured on an anterioposterior (AP) pelvic X-ray. Inclination of the acetabular component will be measured by defining the angle between the tear drop line and the cup. The version of the cup will be measured by using the method described by Lewinnek et al. [22]. Both the cup version and inclination have been proven to have a high inter- and intraobserver reliability and have been proven to be a reliable and valid method when compared to the gold standard. [23–25] Varus and valgus alignment of the stem will be measured by taking the angle between the femoral shaft and the prosthetic component [26]. These measurements will be performed by KR and an independent orthopaedic surgeon. Measurements will be performed on standard outpatient visits six weeks and one year postoperatively. Additionally, amount of blood loss will be calculated from the drop in postoperative blood hematocrit levels, according to the formula of Nadler et al. [27].

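### ANOVA of mean angles, the only test named for component position, cannot detect greater scatter of cup or stem placement in one approach

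*Protocol article*

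**What the plan says.** Under Perioperative measurements, the Protocol article states: "Position of the femoral and acetabular components will be measured on an anterioposterior (AP) pelvic X-ray". Three angles follow. For the cup, "Inclination of the acetabular component will be measured by defining the angle between the tear drop line and the cup", and its version is read by a published radiographic method. For the stem, "Varus and valgus alignment of the stem will be measured by taking the angle between the femoral shaft and the prosthetic component". Films are read at six weeks and at one year.

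Under Statistical analysis, the test for all of these is fixed in one line: "Analysis of Variance (ANOVA) will be used to assess differences in urine incontinence (ICIQ-SF), radiographic measurements, surgical time, blood loss and length of hospital stay", comparing study with control group. No other test is named for the angles. The same section says "Descriptive statistics (means and standard deviations) will be used to describe the subject characteristics and the results of the groups", and that a p-"value of < .05 will be considered to indicate statistical significance".

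The article gives no target angle and no acceptable range. It does not say whether stem alignment is analysed as a signed angle (varus and valgus with opposite signs) or as a magnitude.

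**The concern.** Three of the outcomes in the ANOVA list (surgical time, blood loss, length of stay) have a worse direction, so a comparison of means answers the natural question. An angle of component position need not. Varus and valgus are opposite departures from the shaft axis, and with signed values they cancel in the mean. Cup inclination and version are angles to a reference, not distances from an intended position, so a cup can differ from that position in either direction.

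Two arms can therefore share a mean angle and differ in how consistently the components are placed, and the named test does not look at that difference. At stake is the reading of one secondary outcome: the report could show a single non-significant p-value for cup or stem position although one approach was clearly less consistent. The converse also holds. A small mean shift can be significant when the share of components far from the centre hardly differs.

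**Working it through.** **The plan's own figure.** The article gives no figure for component position. Its one reproducible figure is 60 patients per subgroup for PASS (70% v 90%, 80% power, alpha 5%). The unpooled two-sided formula gives (0.7×0.3 + 0.9×0.1)×(1.96 + 0.84)²/0.2² = 0.30×7.85/0.04 ≈ 59. The arcsine version gives 60 and the pooled version 62, so the figure reproduces. The present point does not depend on it.

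**Inputs from the article.** 120 patients per arm (Sample size calculation) and a 0.05 threshold, taken as two-sided.

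**Assumed inputs, not in the article.** Normally distributed angular error around a common centre. Cup-like case: SD 5 degrees in one arm and 7, 8 or 10 in the other, with a limit of ±10 degrees. Stem-like case: SD 2 v 3 degrees, with a limit of ±5 degrees.

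**Share outside the limit.** P(|X| > L) = 2×[1 − Φ(L/SD)].
- SD 5, L 10: 2×[1 − Φ(2.00)] = 4.6%
- SD 7, L 10: 2×[1 − Φ(1.43)] = 15.3%
- SD 8, L 10: 2×[1 − Φ(1.25)] = 21.1%
- SD 10, L 10: 2×[1 − Φ(1.00)] = 31.7%
- SD 2, L 5: 2×[1 − Φ(2.50)] = 1.2%
- SD 3, L 5: 2×[1 − Φ(1.67)] = 9.6%

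**Equal means, unequal spread.** Share of 10,000 simulated trials with p < 0.05:

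| SDs (limit) | Outside limit | ANOVA, angle | ANOVA, absolute deviation | Chi-square, share outside |
|---|---|---|---|---|
| 5 v 7 (±10) | 4.6% v 15.3% | 5.2% | 92.6% | 83.1% |
| 5 v 8 (±10) | 4.6% v 21.1% | 5.0% | 99.8% | 98.3% |
| 5 v 10 (±10) | 4.6% v 31.7% | 5.4% | 100% | 100% |
| 2 v 3 (±5) | 1.2% v 9.6% | 4.5% | 98.6% | 86.7% |

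A direct test of spread (Brown-Forsythe) behaves like absolute deviation: 92.3%, 99.7%, 100% and 98.4% in the same order. If 10% of the 260 patients are lost, 260×0.9/2 = 117 per arm remain. At SD 5 v 8, 5,000 trials of that size gave 5.6% (angle), 99.6% (absolute deviation) and 97.9% (share outside).

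**Shifted mean, SD 5 in both arms.** For a 2-degree shift the standard error of the difference is 5×√(2/120) = 0.645, so 2/0.645 = 3.10 and power ≈ Φ(3.10 − 1.96) = 87%. The simulation agrees (86.9%). The share outside ±10 moves only from 4.6% to 6.3%, and the two accuracy measures are weak here: 11.6% for absolute deviation and 8.8% for share outside. For a 3-degree shift, ANOVA detects 99.7%. With a 3-degree shift and SD 5 v 8 together, ANOVA detects 93.7%.

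The measures answer different questions: ANOVA of the angle sees a shift, the other two see scatter, and neither replaces the other.

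**The case against.** The strongest reply is that the article never sets out to test accuracy of placement. It records position as one of several perioperative measures, states no accuracy hypothesis, and gives no target. The claims attributed to opponents of the anterior approach in the Discussion concern operative time, blood loss and complications, not malposition. That stands. The premise that a deviation in either direction is an error is natural for a stem around neutral, but for the cup it needs a target that the article does not supply.

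The stem angle may also be meant as an unsigned magnitude. If so, ANOVA already compares mean deviation from neutral, and for the stem the point reduces to stating the convention. That stands too, but it does not help the cup angles.

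A systematic shift is a plausible way for the approaches to differ, since patients lie supine in one arm and lateral in the other, and ANOVA is a sound test for it. This is why the ANOVA should stay.

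Two stronger readings are tempting. A reader might infer that worse accuracy in one approach would go undetected altogether. The article does not support this: a shift would be found, and the SDs will be reported, so unequal scatter would be visible though untested. A reader might also infer that a non-significant ANOVA would be taken as equal placement, but nowhere does the article treat non-significance as equivalence.

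Finally, an analysis plan that is not shown may define derived measures. The choice of ANOVA is nevertheless stated in the article, so it can be assessed as it stands.

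**Conclusion.** The point holds in a limited form. If raw or signed angles are analysed, the one test named for component position has essentially no power against greater scatter around a similar mean: about 5% rejection, while 4.6% v 15% to 32% of components lie outside ±10 degrees. The SDs, limits and normal errors are assumptions. The near-5% rejection does not depend on the particular values, because a test of means rejects at about its nominal level whenever the means are equal. The sizes of the gain from the added measures do depend on them.

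The consequence is confined to a secondary perioperative outcome. The PASS comparison and the sample size are untouched. The change is worth making because it is cheap and uses readings the trial already takes.

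**What to change.** In Statistical analysis, keep the ANOVA of mean angles as the test for a systematic shift, and add the following:

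- State whether stem varus/valgus is analysed as a signed angle and, if so, which direction is positive.
- Compare absolute deviation between groups: for the stem from neutral, for cup inclination and version from a target that the investigators fix before the films are read.
- Compare by chi-square the proportion of components outside a range fixed in advance, separately for each of the three angles.

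No new films or readings are needed. The costs are agreement on cup targets and on ranges for all three angles beforehand, and extra secondary tests: three angles with two measures each, so six per film time analysed. These should be labelled secondary.

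Suggested wording: *Mean cup inclination, cup version and stem alignment (signed; sign convention stated) will be compared by ANOVA. Absolute deviation from a pre-stated target, and the proportion outside a pre-stated range, will be compared between groups as secondary measures of placement accuracy.*
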